### Randomisation

Patients will be randomised in a 1:1 ratio to either the intervention or control arm in the RCT. Random permuted blocks will be used to ensure balance over time. The block size will be kept confidential from the study team until the final database lock. The CRCs will refer to the computer-generated block sequence concealed within sealed opaque envelopes to randomise the patients after obtaining their written informed consent (Fig. 1). Each patient will be assigned an individual randomised study identification number after the randomisation. The number assigned will be used to identify the patient and be used for their documentation in the study file.

### Sample size calculation

We assume a clinically significant difference in HbA1c of 0.5% in the sample size calculation based on data published in previous multicentre randomised controlled trials [14, 15]. For a 1:1 allocation ratio and assuming a standard deviation of 1.4 and 1.3 in the intervention and control arms respectively, a sample size of 115 per arm is required to achieve 80% power to detect a difference in HbA1c of 0.5% based on a two-sided 5% significance level. To account for 30% dropout rate over the 24-month follow up, the total sample size was increased to 165 per arm or a total study population of 330 for the RCT. In the subsequent qualitative study, the tentative plan is to interview 30 patients in the intervention group or more until data saturation is reached [16].

### OPTIMUM telemonitoring system

The OPTIMUM system rides on the cloud-based Philips® *VitalHealth* platform for population health management. The platform is currently being used in more than 100 healthcare networks in countries in North America and Europe and will be launched in Singapore in this study. The study team has leveraged on an innovative strategic approach based on Philips® *Co-Create* methodology to culturally adapt the platform to the local Asian population. The *Co-Create* methodology is a step-wise, iterative, people-centric and multi-disciplinary approach to creative innovation and problem-solving. Based on a mindset of collaboration, it extracts thoughts, intentions, and creative ideas via a facilitated workshop. During the workshop, stakeholders, including the researchers, clinicians, nurses, clinic administrators and patients deliberate with the technical team to develop and culturally adapt both the patient-facing smartphone OPTIMUM app and clinician-facing web-app. Two collaborative interviews were conducted through an iterative process to develop and refine the solution.

The OPTIMUM system was developed after iterative solution refinements and two rounds of user acceptance testing. Both the patient OPTIMUM app and clinician web-portal leverage on the Amazon Web Services (AWS)-hosted cloud solution. The cloud-based, containerised microservice architecture makes it a highly accessible and easily scalable health management solution. It also supports role-based authorisation to allow different clinician roles and for them to have access only to specific patient data set to ensure privacy. It is brand- and system-agnostic to various monitoring devices available in the community.

The OPTIMUM system allows for remote patient monitoring, raises their health and diabetes literacy via locally produced patient education videos, and timely interventions via phone call by the clinicians and nurses in the study team when the patients’ clinical parameters exceed pre-determined thresholds. These thresholds are set by the investigators based on local clinical practice guidelines [17] and are embedded in the OPTIMUM management algorithm. The OPTIMUM system facilitates daily monitoring of patients’ parameters and generates tasks based on pre-defined criteria embedded in the OPTIMUM protocol (Additional file 2). The nurses will also take actions according to the protocol algorithm.

### Intervention

A set of three Bluetooth-enabled devices, a weighing scale (Xiaomi Body Composition Scale 2), a glucometer (Accu-chek Guide set, Model 929 mmol/L) and an electronic blood pressure monitor (Smartfuture Medcheck Blood Pressure Monitor SFB01), will be allocated to each patient in the intervention arm for their sole use during the trial. The CRCs or nurses in the study team will induct these patients to the use of the three devices, and synchronise them with the OPTIMUM app. The patients will use the app to provide their responses to the health assessment questionnaires, which will then automatically transmit the data to the nurses for review.

Patients randomised to the control arm will continue with standard care as described previously and may continue using their own devices, if any, for their own monitoring. Patients randomised to the intervention arm are expected to perform the following tasks in the first 6 months after recruitment (Fig. 2).

**Fig. 2 Fig2:**
[figure not shown]
OPTIMUM treatment algorithm

#### Tele-education

For a period of eight consecutive weeks post-enrolment, patients will receive weekly push reminders for self-monitoring via the OPTIMUM app, links to educational videos covering various aspects of T2DM management (understanding T2DM, eating healthily, alcohol and smoking advice, physical activity demonstrations, and having a healthy mindset). These videos aim to empower patients to improve their self-management of T2DM. After viewing each video, each patient will take a short quiz to test their knowledge related to the video content via the app.

#### Tele-monitoring and tele-support

Patients will self-monitor their body weight, blood pressure, heart rate and capillary glucose levels using the devices according to the stipulated schedule in the OPTIMUM system. The readings will be automatically transmitted through the OPTIMUM system to the clinical care team who will review them asynchronously using the clinician-facing dashboard. Personal target thresholds are pre-set based on clinical practice guidelines (Additional file 2). The study team nurses will phone the patients based on the OPTIMUM treatment algorithm to assess, advise and manage patients accordingly based on their clinical parameters.

Patients will receive immediate feedback via push notifications from the app if their clinical parameters deviate beyond the stipulated range. They will be prompted to respond to questions in the messages to verify their measurements, screen for any related symptoms and assess adherence to medications. The nurses will review their responses before deciding on the appropriate actions based on the pre-specified escalation protocols. The actions include telephone consultations or arranging for patients to return to the polyclinic for assessment in consultation with the clinicians. Patients will also be encouraged to contact the nurses should they have queries about their chronic conditions.

#### Qualitative study procedure

Patients from the intervention arm will be purposively selected from both gender, age and ethnic groups and different level of self-care behaviour (based on their scores in the various scales) to participate in interviews. The one-to-one in-depth interviews will gather qualitative data on their experiences, utility and adherence to self-monitoring using the devices and the OPTIMUM system. Each interview will be audio-recorded, transcribed and audited by an assigned investigator. The topic guide is available as Additional file 3.

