Telemedicine refers to the systematic provision of healthcare services over separate environments via ICT [9]. In Singapore, it is categorised into tele-collaboration, tele-treatment, telemonitoring and tele-support [9]. A meta-analysis has shown that telemedicine (used interchangeably with telehealth) is effective in improving glycaemic and blood pressure control [10]. However, the selected trials enrolled subjects with baseline HbA1c levels of above 9%, which is skewed towards a subset of high-risk patients and may not be generalisable to others with better glycaemic control. Other limitations include lack of differentiation of the various components of telemedicine and that the study populations were mostly Caucasians. The findings may not be entirely translatable to Asians due to varying levels of acceptance of telemedicine. Sin et al. have shown that only 52% of local patients in polyclinics were willing to use telemonitoring to support their self-management of T2DM and/or hypertension [11]. The construct and design of the telemedicine system need to be patient-centric and culturally-adapted to increase uptake before assessing its outcomes.

A team of primary care professionals have teamed up with a multinational telemedicine vendor to create a telemonitoring system leveraging on the latter’s *VitalHealth* population health platform. Design-thinking, which includes patients’ input, was deployed in developing the telemonitoring system, embedded with educational material, such as locally produced video on T2DM management and evidence-based management algorithm. The system is named OPTIMUM – “*O*ptimising care of *P*atients via *T*elemedicine *I*n *M*onitoring and A*u*gmenting their control of Diabetes *M*ellitus”.

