#### Inclusion criteria

Diagnosis of T2DM in the patient’s electronic medical record (EMR),Latest glycaemic control based on HbA1c reading between 7% and 10%,Age between 26 and 65 years,No or only mild non-proliferative diabetic retinopathy without any macular involvement,Renal function: estimated glomerular filtration rate (eGFR) of 45 ml/min/1.73 m^2^ or higher (up to stage 3a classification of chronic kidney disease) [13],Non-smokers, or ex-smokers who have quit smoking for at least 12 months,Willingness to download the OPTIMUM smartphone application (app),Willingness to use the standard monitoring devices (blood pressure set, glucometer and weighing scale) which will synchronise with the OPTIMUM telemonitoring system according to the study protocol throughout the 6-month study period,

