#### Exclusion criteria

Poorly controlled glycaemic control based on the latest HbA1c reading of more than 10%.Cognitive impairment based on a diagnosis of dementia or mild cognitive impairment in the EMR.Pre-existing retinal pathologies documented in the EMR: proliferative diabetic retinopathy (moderate to severe) or other retinal and macular or diseases.Pre-existing chronic kidney disease stage 3b, 4 or 5.Known peripheral vascular, coronary and cerebrovascular disease.Individuals with any end-stage disease with life prognosis of less than 2 years.Pregnant women.Self-declared reluctance or inability to commit to the entire study over 24 months.Self-declared reluctance to use the OPTIMUM smartphone app and the associated monitoring devices.Current enrolment in another trial involving therapeutic or non-therapeutic intervention which will interfere with the primary and secondary outcomes in this study.

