#### Secondary outcomes at stipulated time points

Post-intervention HbA1c at 12 and 24 months.On-site systolic and diastolic blood pressure readings.Weight and BMI.Absolute and change in scores in EQ. 5D-5L, MARS-5, MPR, MDKT, SCI, IPAQ-SF, PAID.Healthcare utilisation based on hospitalisation and polyclinic treatment bills.Incidence of macro and microvascular complications, such as coronary, cerebral, renal retinal and peripheral vascular diseases diagnosed by clinicians and documented in the EMR. Renal outcomes will be determined from the serum creatinine, urine albuminuria and eGFR.Fidelity of patients to the stipulated telemonitoring protocol. It will be computed based on the proportion of them adhering to or exceeding the recommended frequency of self-monitoring of the three key clinical parameters (systolic and diastolic blood pressure, weight and capillary blood glucose) and the proportion of them who have viewed all the health education videos. These data will be retrieved directly from the OPTIMUM system.

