## Discussion

Appropriate management of T2DM is crucial in mitigating its associated morbidity and mortality. Current models of care of TD2M patients is episodic and often resource intensive. Gaps in monitoring patient between visits exist and continuity of care is key to optimising glycaemic control.

Telemedicine is promising in how care delivery can be modified to improve glycaemic control through continuous monitoring of patients by leveraging on ICT.

The OPTIMUM programme is a novel multicomponent primary care telemedicine programme comprising of remote patient monitoring, education, and timely interventions utilising a bespoke patient-facing smartphone application and clinician-facing web application. The OPTIMUM *VitalHealth* system is culturally adapted through an iterative and collaborative process in close consultation with clinicians, patients and technical staff.

While previous studies have shown a positive impact of telemedicine in the treatment of T2DM patients, baseline characteristics of these patients were largely poorly controlled. Furthermore, these previous studies were done in a Western population which may not be generalizable to an Asian population. We will thus determine the effectiveness and acceptability of a culturally adapted telemedicine in supporting standard of care of T2DM patients.

Findings from this study will enable provide insight into the acceptability of such a model of T2DM and possibly chronic diseases as a whole. It will also better inform policy makers in adopting telemedicine for population health management.

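### Interviewees are varied by questionnaire scores and not by logged use of OPTIMUM, so reasons for disengaging may go unheard, and the acceptability conclusion reaches beyond the willing patients enrolled

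*Protocol article*

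**What the plan says.** All places are in the protocol article.

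- **Aim.** The last paragraph of Background limits the qualitative aim to patients in the intervention arm: their experience, their acceptance of OPTIMUM and how useful they find it.
- **Sampling.** Qualitative study procedure selects interviewees purposively by gender, age and ethnic group, and by "different level of self-care behaviour (based on their scores in the various scales". The interviews are to cover experience, utility and adherence to self-monitoring with the devices and the system.
- **Number.** Sample size calculation gives a tentative 30 interviews, or more until saturation.
- **Use data.** Secondary outcomes defines fidelity as the proportion of patients who meet the monitoring frequency and the proportion who view all the videos. It adds: "These data will be retrieved directly from the OPTIMUM system".
- **Entry.** Inclusion criteria require "Willingness to download the OPTIMUM smartphone application (app" and "Willingness to use the standard monitoring devices (blood pressure set, glucometer and weighing scale". Exclusion criteria remove patients with "Self-declared reluctance to use the OPTIMUM smartphone app and the associated monitoring devices" and with "Self-declared reluctance or inability to commit to the entire study over 24 months".
- **Known uptake.** Background cites a local study in which "only 52% of local patients in polyclinics were willing to use telemonitoring".
- **Reach of the conclusion.** Discussion says the findings will "provide insight into the acceptability of such a model of T2DM", possibly of chronic disease care as a whole, and will inform policy makers on population health management.

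**The concern.** There are two separate mismatches.

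First, the behavioural variable used to pick interviewees is not the behaviour the interviews are about. A patient may score well on self-care or medication adherence and hardly open the app, or score poorly and use it daily. Varying the scores does not ensure a spread of system use. Patients who used the system little or gave it up are the best informed about why it was not accepted. If none is sought, the interviews can reach saturation among engaged users, and the account of acceptance will tend to be favourable.

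Second, everyone interviewed had agreed before randomisation to use the app and devices. What they say cannot represent patients who would have refused, yet the Discussion speaks of the care model in general. A policy reader could take the result as covering polyclinic patients at large.

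**Working it through.** The article states no figure for this point, so the check sets its sections side by side.

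**1. Do the scales measure system use?** The instruments under the heading on T2DM-related literacy and behaviour profiles are:

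| Instrument | What it is described as measuring |
|---|---|
| EQ-5D-5L | health status |
| MARS-5 | adherence to oral medication |
| MPR | insulin supply relative to days in the study |
| MDKT | diabetes knowledge |
| SCI | perceived self-care, especially adherence to prescribed treatment |
| IPAQ-SF | physical activity |
| PAID | diabetes-related distress |

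None is described as measuring use of OPTIMUM. SCI and MARS-5 come closest, and both rest on the patient's own report of general self-care or medicine-taking.

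**2. Is a better variable available?** Yes. The fidelity outcome draws on the system's own record of monitoring frequency and videos viewed. It concerns the same behaviour as the interview topic and is held for the same patients. Qualitative study procedure does not name it for sampling.

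**3. Are low users and leavers excluded?** No. Sampling is from the intervention arm, with no restriction to retained or active users. They are also not sought. For drop-outs, Demographic and clinical data states only that demographic data are collected and compared with those of trial participants. That can show who left, but not why.

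**4. Can the stopping rule protect against this?** Not by itself. Saturation means that further interviews add no new themes within the kind of patient being sampled. If patients who disengaged are not among them, saturation can be reached without their themes.

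**5. Does the conclusion match the sample?** The aim in Background does: it is confined to the intervention arm. The Discussion does not: it moves to the care model, possibly to chronic disease generally, and to policy. The entry criteria in between restrict the sample to willing patients. The article's own citation of 52% willingness shows that unwilling patients are not a negligible group locally.

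**6. Does any trial figure change?** No. The article's 165 per arm is 115 / (1 − 0.30) = 164.3, rounded up, and does not depend on the interviews.

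**The case against.** The strongest reply is that the design fits its stated aim. The qualitative aim concerns the intervention arm only, and patients unwilling to use an intervention cannot sensibly be randomised to it. Willingness is therefore an ordinary limit on generalisability. This stands as far as the entry criteria and the aim are concerned. It does not cover the wider wording of the Discussion.

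Next, seeking different levels of self-care will bring in some patients who manage poorly, and unfavourable themes can still emerge. This also stands, and it is why the direction of bias is likely and not certain. Non-use will moreover be counted through the fidelity outcome. That is true, but a count does not explain why patients disengage, which is what interviews are for.

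A fuller sampling plan may exist outside the article, and the topic guide is in an additional file not shown. However, the article does state its sampling variables, and the point rests on those.

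A reader might infer three stronger things that the document does not support.

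- **A numerical overstatement.** Suppose 80% of enrolled patients found the system acceptable (an assumption) and 52% of the population were willing. Then 0.52 × 0.80 = 0.416, about 42%, but only if no unwilling patient would find it acceptable. If unwilling patients accepted equally, 0.52 × 0.80 + 0.48 × 0.80 = 0.80, and there is no overstatement. Purposive interviews estimate no acceptance rate in any case. The 52% concerns telemonitoring in general, among patients with diabetes and/or hypertension, and is cited as the reason for building an adapted system.
- **A number of patients missed.** 0.30 × 165 = 49.5, about 50, but the 30% allows for trial drop-out over 24 months, whereas the intervention lasts 6 months. Leaving follow-up later is not abandoning the app, and drop-outs are not barred from interview.
- **Interviews too late to reach those who stop.** Study design says the qualitative work follows the trial, but the SPIRIT table gives interviews their own time point, and its placement is not visible in the text available. The timing cannot be judged.

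**Conclusion.** The point holds as a cheap improvement. Interviewees are varied in behaviour only through questionnaire scores that do not measure use of OPTIMUM, while logged use is already to be retrieved. Patients who used the system little or stopped are untargeted, not excluded. The account of acceptance is therefore likely to be too favourable, on the assumption that those who disengage hold less favourable views and are under-represented unless sought. The size of that effect cannot be worked out from the article.

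Separately, and by design, the findings apply to patients willing to use the app and devices. The willingness criteria are not a fault for the stated aim. The only part to correct is the Discussion's extension to the care model and to policy. The randomised comparison, the sample size and the error rates are unaffected.

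**What to change.** 1. **Qualitative study procedure.** Add logged fidelity (high, partial, and minimal or stopped use) as a sampling stratum beside gender, age, ethnic group and self-care scores. Keep the scores, because replacing them would lose planned variation in self-care.
2. **Same section.** State that patients who stopped using the app or left the trial, and who consent, will be invited for interview. Keep the plan of 30 interviews or more until saturation, without a cap.
3. **Discussion.** Word the acceptability conclusion for patients willing to use the system. Ideally, report beside it the number of otherwise eligible patients not enrolled because of reluctance about the app or devices.

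The cost is small, since the strata come from data the study will already hold. Some patients who stopped will decline an interview, so recruiting them will take slightly longer. The optional count needs the reason for non-enrolment to be noted at screening.

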### Data

#### Demographic and clinical data

Patients’ sociodemographic and clinical data will be recorded using questionnaires (Table 1). They include age, gender, ethnicity, housing type, employment status, marital status, household information, household monthly income, citizenship and education level; year of diagnoses and duration of T2DM, hypertension, dyslipidaemia, post-enrolment onset of T2DM-related macro, microvascular complications such as coronary, cerebral and peripheral vascular diseases retinopathy, nephropathy, neuropathy, foot complications and hypoglycaemia; adverse events such as hypoglycaemia, hypotension and lifestyle behaviour such as alcoholic intake.

The CRCs will measure their clinical parameters according to the protocol schedule, including systolic and diastolic blood pressure, pulse rate, weight, height and body mass index (BMI).

Demographic data as above will also be collected for participants who drop out and analysed with trial participants for any differences.

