### Setting and participants

The trial will be conducted at a polyclinic located in Sengkang, an estate in north-eastern Singapore with a population of about 300,000 multi-ethnic Asian residents [12]. This polyclinic serves approximately 900 to 1000 patients daily during office hours in each weekday and is similar to the other polyclinics in Singapore [11]. Current standard of care of patients with T2DM at polyclinics include 3–6 monthly doctor’s consultation with HbA1c readings; fasting laboratory panel tests (electrolyte panel, lipid panel, liver panel and urine albumin-creatinine ratio) at diagnosis and then every 6 to 12 months; and annual diabetic retinal photograph and diabetic foot screening. Patients may be referred to dieticians for dietary advice, nurses for co-management or onwards to tertiary care specialists at the discretion of the attending physician.

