### Statistical analysis

Baseline characteristic (e.g. demographics and socioeconomic status, medical history and lifestyle etc.) will be summarised by arm. The Kolmogorov–Smirnov test will be applied to evaluate the normality of data distribution. For continuous variables, mean and standard deviation will be reported if they are normally distributed, otherwise median and interquartile range will be reported. The number of cases and proportions will be reported for categorical variables.

Continuous outcomes, including mean HbA1c, systolic and diastolic blood pressure, BMI, quality of life, medication adherence and rating scales will be compared by arms. Mean difference with 95% confidence interval will be calculated and tested by two sample *t* test if they are normally distributed, and the non-parametric test will be applied otherwise. The number and proportion of patients experiencing a cerebrovascular event will be tabulated by arm. Difference in proportions will be tested using Fisher’s exact test with 95% confidence interval calculated. One interim analysis with the same abovementioned analyses is planned for this trial when all the patients complete month 6’s follow-up visit. The level of significance will be set at 5%. Data will be analysed using Statistical Analysis System v.9.4.

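### For dropouts the article names demographic data and an unadjusted test on observed HbA1c, and neither protects the comparison from selective loss

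*Protocol article*

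**What the plan says.** - **Dropouts** (Protocol article, Demographic and clinical data): "Demographic data as above will also be collected for participants who drop out and analysed with trial participants for any differences". HbA1c is not in the list this sentence refers back to; it appears in the next subsection, Laboratory data.
- **Test** (Statistical analysis): "Mean difference with 95% confidence interval will be calculated and tested by two sample" t test if the data are normal, and by a non-parametric test otherwise. No baseline covariate is named.
- **Size** (Sample size calculation): "a sample size of 115 per arm is required to achieve 80% power". Then, "To account for 30% dropout rate over the 24-month follow up", the number rises to 165 per arm, 330 in total.
- **Time point** (Primary outcome measures): HbA1c at 6 months is primary. The 12- and 24-month values are secondary. No loss rate is given for month 6.
- **Routine data** (Setting and participants): standard care includes a 3–6 monthly "consultation with HbA1c readings". Medical records already supply data around recruitment (notes to Table 1) and the complication outcomes (Secondary outcomes).

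**The concern.** A demographic comparison can show whether those who left differ in age, income or ethnicity. It does not recover an outcome or change an estimate. Balanced demographics are also compatible with loss that depends on how HbA1c responded, and that is the kind of loss that biases the result.

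Selective loss is plausible here. The trial is open-label, and only the intervention arm has the self-monitoring, prompts, quizzes and nurse calls. Patients who tire of these without improving may leave, which would flatter the intervention. Equally, control patients disappointed not to receive the app may leave, and the bias could then run the other way.

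Whether outcomes are sought after a patient stops has to be settled, with suitable consent, while the trial runs. A later analysis plan cannot use values that nobody obtained.

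**Working it through.** **1. The article's own figures.** Inputs from Sample size calculation: difference 0.5, SDs 1.4 and 1.3, two-sided 5%, power 80%.

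n per arm = (z₀.₉₇₅ + z₀.₈₀)² × (1.4² + 1.3²) / 0.5² = 7.849 × 3.65 / 0.25 = 114.6, so 115.

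Power at 115 per arm is 80.1% by the normal approximation and 79.8% by the noncentral t. Inflation: 115 / (1 − 0.30) = 164.3, so 165 per arm. The sample size is correct. The inflation protects power; it does nothing about bias.

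**2. Bias of an observed-values comparison.** Let d be the share of an arm without a value, and g the mean HbA1c of those patients minus the mean of those observed (positive means worse). In each arm, mean of all randomised = observed mean + d × g. Subtracting the arms:

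bias in favour of the intervention = d_I × g_I − d_C × g_C.

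**3. Range.** The documents give neither d at month 6 nor any g, so every row is an assumption.

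| Loss, intervention / control | Gap, intervention / control | Bias (HbA1c points) | Share of 0.5 |
|---|---|---|---|
| 30% / 30% | 0.5 / 0.5 | 0.15 − 0.15 = 0 | 0% |
| 20% / 10% | 0.3 / 0.3 | 0.06 − 0.03 = 0.03 | 6% |
| 20% / 10% | 0.8 / 0.8 | 0.16 − 0.08 = 0.08 | 16% |
| 10% / 20% | 0.3 / 0.3 | 0.03 − 0.06 = −0.03 | 6%, against the intervention |
| 10% / 20% | 0.8 / 0.8 | 0.08 − 0.16 = −0.08 | 16%, against the intervention |
| 10% / 10% | 0.5 / 0 | 0.05 − 0 = 0.05 | 10% |
| 15% / 15% | 0.5 / 0 | 0.075 − 0 = 0.075 | 15% |
| 30% / 30% | 0.5 / 0 | 0.15 − 0 = 0.15 | 30% |

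Equal loss alone is not enough for zero bias; the gaps must match too (sixth to eighth rows).

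**4. Effect on the test.** With no true difference and the SDs unchanged, the two-sided 5% test rejects 6.2% of the time for a bias of 0.05 with 148 per arm (10% loss), 7.5% for 0.075 with 140 per arm (15% loss), and 13.4% for 0.15 with 115 per arm (30% loss). The last case belongs with the 24-month comparison, the only horizon for which 30% is stated.

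**5. What the demographic comparison adds.** The bias depends on g, a difference in an unobserved outcome. A demographic comparison measures differences in other variables. It can raise suspicion, but it neither estimates g nor removes d × g.

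**The case against.** The strongest defence is that this is a condensed article. The full protocol or analysis plan may define the analysis set and the handling of missing values, and their absence here is no fault. That stands, and the point does not rest on it. It rests on what the article does name for dropouts and for the test.

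Four stronger readings are tempting, and the documents do not support them.

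- **That nothing but demographics will be collected, so the primary result is a completers' comparison.** The sentence says demographic data will *also* be collected, which does not rule out HbA1c follow-up. No analysis set is stated. A patient who leaves between months 6 and 24 still contributes a month-6 value.
- **That 30% will be missing from the primary comparison.** The 30% covers 24 months.
- **That most of the missing values already sit in the records.** Standard care includes regular HbA1c, but Background reports defaulting and use of multiple providers. Patients who leave the trial may also leave care, and withdrawn consent may bar access.
- **That retrieval lifts power from about 80% to 89%.** Those figures belong to 115 and 148 patients per arm, that is to 30% and 10% loss. If month-6 loss is 10%, the existing plan already has 148.

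It is also fair that differential loss is not shown. Both arms follow the same visit schedule, vouchers go to every participant, and patients unwilling to use the app or to commit to 24 months are excluded before randomisation. Stopping the app is not the same as missing a visit. These features make large differential loss less likely but do not exclude it.

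**Conclusion.** The point holds in a limited form. The measures the article names do not protect the HbA1c comparison against selective loss, and a better analysis is available at low cost. At month 6 the bias is probably modest: 0.03 to 0.08 points (6% to 16% of the 0.5 target) for a 10-point difference in loss and gaps of 0.3 to 0.8 points, in either direction, and zero if loss and gaps are equal across arms. It could be larger at 24 months, where the planned loss is 30%. Loss rates, gaps and direction are all assumed. The sample size is not in question. The change is worth making; confidence is medium, because the full protocol may already provide for outcome follow-up.

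**What to change.** 1. **Collect.** State that HbA1c at months 6, 12 and 24 will be sought for every randomised patient, including those who stop the app or the study visits. Where a visit is missed and consent allows, take the routine record value within a fixed window around the time point, the same in both arms.
2. **Analyse.** Keep all patients in their randomised arm. Replace the visit-by-visit test for HbA1c by one repeated-measures model with arm by visit and baseline by visit, and read the month-6 contrast as primary. The model does not replace step 1: a patient with no HbA1c after baseline adds nothing to the contrast.
3. **Test the assumption.** For values still missing, add a delta-shift analysis that makes them worse by a stated range, separately by arm. Keep the demographic comparison as description only.

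The cost is some consent and protocol wording, record extraction, and one model in place of several tests. The downsides are wider timing windows for retrieved values and some dropouts for whom no routine value exists.
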